
**Fig. 4 Fig4:**
[figure not shown]
Measurement of ROM

**Fig. 5 Fig5:**
[figure not shown]
Schematic of three-dimensional gait analysis and shear wave elastic imaging technology analysis. (I) Three-dimensional gait analysis of the participants; (II) three-dimensional data of the knee; (III) shear wave elastic imaging technology analysis performed by doctors. For the labels in II. **A** anterior/posterior displacement; **B** superior/inferior displacement; **C** internal/external displacement; **D** internal/external flip angle; **E** external/internal rotation angle; **F** flexion/extension angle. (By Figdraw https://www.figdraw.com/.)

#### Assessment of safety

To evaluate the safety of treatment, the proportions of participants with adverse reactions in each group (T) are calculated. Adverse events are recorded and handled throughout the treatment and follow-up periods. According to previous literature and clinical experience, complications of FSN include subcutaneous hematoma, subcutaneous hemorrhage, and acupuncture syncope [39–41]. A clinical study reported that 5.36% of participants experienced mild subcutaneous hemorrhage or hematoma at the operating site of FSN treatment [39]. One RCT reported a 3.84% incidence of acupuncture syncope and a 3.84% incidence of subcutaneous hematoma in the FSN group [40]. In another RCT, 2.22% of participants in the FSN group experienced acupuncture syncope, while 4.44% had subcutaneous hemorrhage [41]. However, the clinical symptoms of these complications or adverse reactions were mild, and no serious cases were reported. For these minor complications, management strategies were generally simple, and patients recovered completely in a short time without sequelae. Regarding the potential risk of infection caused by FSN, no literature has clearly reported the occurrence, nor has any literature statistically analyzed the incidence. However, since the needle is inserted into the subcutaneous layer, there is a possibility of local skin infection even though the skin has been sterilized in advance. Should an infection occur, the needle is removed immediately. In consultation with the dermatology department, skin care, etiological testing, and appropriate antibiotics are administered if necessary. For the administration of celecoxib, possible complications and adverse effects include gastrointestinal reactions, renal insufficiency, rashes, etc. [42, 43]. The complications are recorded during medication and at follow-up visits, and reported to the the researchers immediately. Any complication is documented using a preset questionnaire, and appropriate measures are taken accordingly. If a more serious adverse reaction develops and the investigator considers the participant unfit to proceed with the study, the experimental interventions for this participant will be promptly terminated.

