### Study setting

Participants are recruited from the outpatient department of Guangdong Provincial Hospital of Chinese Medicine. Eligible and consented participants are randomly assigned at a ratio of 1:1 to receive treatment in the FSN group (n = 30) or drug group (n = 30) for 2 weeks. Participants are assessed at baseline and on the 7th, 14th, 28th, and 42nd days after the start of the intervention. The design of the trial is summarized in Fig. 1.

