### FSN therapy

Operation of the FSN follows the KOA’s Fu’s Subcutaneous Needling Treatment Code of Practice [27]. Participants first assume the supine position. After routine disinfection, a disposable Fu’s subcutaneous needle (Nanjing Paifu Medical Technology Co., Ltd., Jiangsu, China, Fig. 2) is inserted parallel into the subcutaneous loose connective tissue around the pathological tight muscles (gastrocnemius muscle, tibialis anterior muscle, and quadriceps femoris muscle). The protruding part of the hose holder is fixed to the card slot after the needle is completely inserted. Confirming that the participants have no pain, the index and ring fingers alternate back and forth in a smooth, soft, fan-like swaying movement. The fan angle is approximately 60°, and a total of 45 round trips are performed in 30 s. Swaying Movement is accompanied by Reperfusion Approach: 20 sways along with 10 s of Reperfusion Approach are performed as a set of procedures. For each target pathological tight muscle, 2–3 sets of the above procedures are required. The Reperfusion Approach for different pathological tight muscles are as follows: (1) for the gastrocnemius muscle, the participant is placed in the prone position, with the foot extended out of the bed. A towel is placed on the soles of the feet, and the participant is instructed to resist resistance by plantar flexion of the ankle joint; (2) for the tibialis anterior muscle,the participant is placed in the supine position, and the ankle is dorsiflexed to resist counterdirectional forces from the instructor, (3) for the quadriceps muscle,the participant is placed in the supine position. With a foam shaft or other support made of soft material placed in the popliteal fossa, the knee joint is then forcefully extended against resistance from the instructor. The FSN group is treated 3 times a week for 2 weeks. Prior each FSN treatment day, participants are contacted by telephone in advance to schedule specific sessions and are reminded to attend. (Fig. 3).

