### Oral celecoxib

Participants in the drug group receive 200 mg of oral celecoxib (a capsule) daily for 2 weeks. They are required to mark prepared schedules after each dose. After the seventh and fourteenth doses, participants return to the research center with their schedules for review. They are closely followed up during the administration of the drug, and the treatment will be discontinued immediately in case of adverse events. If necessary, appropriate symptomatic treatments, such as acid suppressing, protection of the gastric mucosa, anti-vertigo medication, etc., will be administered until the adverse events subside.

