## Discussion

This study evaluates the effectiveness of FSN for the treatment of senile knee osteoarthritis compared to that of NSAIDs in terms of pain, self-reported function, gait, and muscle flexibility and assesses the differences in adverse events between the two interventions.

The main therapeutic objectives of KOA are to reduce pain, improve knee function, control arthritic symptoms, and enhance patients’ quality of life. In addition to weight loss and functional knee exercises, NSAIDs are consistently recommended by all guidelines as the first-line therapeutic agent to relieve pain [44, 45]. However, long-term application of NSAIDs carries the risks of gastrointestinal bleeding, cardiovascular adverse events, and nephrotoxicity. In addition, symptoms tend to recur once the drug is discontinued. For the elderly population, the risk of adverse reactions caused by NSAIDs is even greater. For example, the incidence of upper gastrointestinal bleeding is greater than that of other age groups, and the extent of the lesions is more severe [42, 43]. In the early or middle stage of KOA, to prevent the disease from progressing to an advanced stage that is difficult to reverse, clinical guidelines in various countries recommend treatments such as appropriate physiotherapy and muscle functional training, which aim to correct the pathological biomechanical imbalance of the affected knee joint [46, 47]. Therefore, in addition to medication, aggressive early intervention with complementary therapies for KOA may be of important.

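### The safety measure is worded as adverse reactions, while the trial records, and says it compares, adverse events; the calculated measure should be all-cause

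*Protocol article*

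**What the plan says.** The protocol article (Assessment of safety) sets the calculated measure: "the proportions of participants with adverse reactions in each group (T) are calculated". The next sentence describes the data: "Adverse events are recorded and handled throughout the treatment and follow-up periods". Table 1 likewise schedules adverse events at day 7, day 14 and follow-up. The Discussion states the aim, which is that the study "assesses the differences in adverse events between the two interventions".

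Contact during treatment is described separately by arm. For FSN: "The FSN group is treated 3 times a week for 2 weeks", and before each treatment day "participants are contacted by telephone in advance to schedule specific sessions and are reminded to attend". For celecoxib: "After the seventh and fourteenth doses, participants return to the research center with their schedules for review", and also "They are closely followed up during the administration of the drug", with no frequency or mode given. Both arms share the scheduled assessments (Study setting): "Participants are assessed at baseline and on the 7th, 14th, 28th, and 42nd days after the start of the intervention".

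Under Randomization and blinding, participants and practitioners are unblinded, while outcome assessors and those who collect and analyse the data are blinded. The safety section adds a preset questionnaire and immediate reporting of complications. Neither is described as differing by arm.

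**The concern.** An adverse event is anything untoward that happens. An adverse reaction, in ordinary usage, is the subset judged to be caused by treatment. If the plan is followed as worded, the arms are compared on the subset although the stated aim concerns the whole.

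The distinction matters more than usual here. The people closest to each event, the participant and the practitioner, know the treatment. The FSN harms that the article lists (local bleeding or hematoma, and syncope with needling) are local or immediate and easily linked to the procedure. The listed celecoxib harms (gastrointestinal reactions, rashes, renal insufficiency) are less specific in people aged 60 to 80 and can be attributed either way. A count that passes through that judgement may differ between arms for reasons other than risk.

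A second issue is the opportunity to notice events, since scheduled attendance during treatment is more frequent in the FSN arm. The Discussion supports complementary therapy partly by reference to NSAID risks in the elderly, so the safety comparison is likely to be cited when the result is interpreted.

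**Working it through.** The article gives no safety rate, power or contact count, so there is no stated figure to reproduce. The check compares the statements and then asks how large the effects could be.

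**1. The statements side by side**

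| Place | Term | Role |
|---|---|---|
| Assessment of safety, first sentence | adverse reactions | calculated |
| Assessment of safety, second sentence | adverse events | recorded |
| Table 1 | adverse events | scheduled |
| Discussion, opening | adverse events | compared |

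Three of the four agree, and the one that defines the calculation differs. Elsewhere in the article the word reaction leans towards a causal sense: the Discussion uses it for harms caused by NSAIDs, and the safety section uses it for harms ascribed to FSN. The safety section also uses complications and adverse effects without defining either.

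**2. What attribution could do**

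Assume a true adverse-event risk of 20% in both arms, so 30 × 0.20 = 6 participants per arm.
- If 80% of FSN and 40% of drug-arm events are attributed: 6 × 0.8 = 4.8 against 6 × 0.4 = 2.4.
- With the fractions reversed: 2.4 against 4.8.

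The risk and the fractions are assumptions. They show only that the direction is not fixed.

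**3. Contacts during treatment**
- FSN: 3 per week × 2 weeks = 6 sessions. Drug arm: 2 stated returns. Ratio 6/2 = 3.0.
- If the day-7 and day-14 assessments are extra visits for FSN: 8/2 = 4.0.
- If the drug arm's close follow-up adds, say, 2 contacts: 6/4 = 1.5, or 8/4 = 2.0.

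Telephone calls before FSN sessions would raise the ratio if they were counted.

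**4. What unequal contact could do**

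Assume equal true risk, capture only at contacts, and a chance c of capture at each contact. The share detected after k contacts is 1 − (1 − c)^k. Counts are out of 30 at a true risk of 20%.

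| c | FSN, k = 6 | Drug, k = 2 | Ratio | Expected counts |
|---|---|---|---|---|
| 0.1 | 0.469 | 0.190 | 2.47 | 2.8 vs 1.1 |
| 0.3 | 0.882 | 0.510 | 1.73 | 5.3 vs 3.1 |
| 0.5 | 0.984 | 0.750 | 1.31 | 5.9 vs 4.5 |
| 0.8 | 1.000 | 0.960 | 1.04 | 6.0 vs 5.8 |

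The article gives no c. Recall at the common visits and immediate reporting both work against the assumption that capture happens only at contacts.

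**5. Scale**

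One participant is 1/30 = 3.3 percentage points of an arm. The FSN complication rates that the article cites, 2.22% to 5.36% for single complications, correspond to 30 × 0.0222 = 0.7 up to 30 × 0.0536 = 1.6 participants. Counts will be small whichever definition is used.

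**The case against.** The strongest reply is that the causal reading is inferred. No causality rule, scale or assessor is stated, several terms are used interchangeably, and the very next sentence says adverse events. Loose wording is a plausible explanation, and a condensed article may leave definitions to a fuller document. This stands as far as intent goes: a reader might infer that the trial applies a causality judgement made with knowledge of the arm, and the article does not say so. It does not remove the mismatch between what is calculated and what is said to be compared.

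A reader might also infer from the 6-to-2 count that the comparison is distorted. The article does not support that. The count covers only scheduled in-person attendance. The drug arm is also closely followed, both arms share the assessment days, a preset questionnaire and immediate reporting apply, and assessors and data collectors are blinded. Blinded collection may be imperfect with unblinded participants, but it is a real safeguard.

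Three further points are fair. The 3.3-point step applies to any binary measure with 30 per arm, including the one proposed below. The cited FSN complications are the events least open to dispute over cause, so their small expected numbers do not by themselves show sensitivity to attribution. The Discussion's NSAID argument concerns long-term use, whereas treatment here lasts 2 weeks and no safety hypothesis is stated.

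**Conclusion.** The point holds in a limited form. As worded, the safety measure is the proportion with adverse reactions, while the data recorded and the comparison claimed concern adverse events. Taken literally, the measure depends on attribution in a trial with unblinded participants and practitioners, and it does not estimate the stated comparison. This rests on the ordinary meaning of the term; if the wording is merely loose, a correction of wording is all that is needed.

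Unequal scheduled contact is a possible source of ascertainment bias of unknown size. Under the assumptions shown, it runs from almost nothing (ratio 1.04) to more than twofold (2.47), and existing safeguards partly reduce it. An attribution effect could favour either arm. Neither bias has been shown to occur.

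**What to change.** In Assessment of safety, change the calculated measure to the proportion of participants in each arm with at least one adverse event, regardless of causality. Base it on the existing preset questionnaire, completed at the common assessments on days 7, 14, 28 and 42 in both arms. Tabulate separately (a) treatment-related reactions and (b) events first noted at FSN sessions between those assessments, so that the effect of extra contact can be seen.

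The cost is a change of wording, because the visits and the questionnaire already exist. The all-cause proportion will be higher in both arms than a reactions-only figure. The change removes the main measure's dependence on attribution. It reduces but does not remove the effect of unequal contact, since minor unrelated events can also be picked up at additional visits.

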### Statistical analysis

All the statistical tests are conducted using a bilateral test, with *P* < 0.05 indicating a statistically significant difference. The Mean ± standard deviation is used for normally distributed measurement data. Non-normal data are presented as the median and interquartile range. Differences in data on outcome measures from baseline to each evaluation time point are analyzed using independent sample t tests or Mann–Whitney U tests, as appropriate, between groups; paired t tests or Wilcoxon tests are used to compare differences in the data for each outcome index at each evaluation time point within the group. In addition, the VAS and WOMAC evaluations are repeated 5 times in this study. Therefore, repeated measures analysis of variance are used for auxiliary analysis. Baseline data (including age, sex, BMI, etc.) are controlled for as confounding factors. Multiple imputation methods are adopted for the analyses of missing data. A generalized linear mixed model is further used for analyses of non-normal and partially missing data, as the interaction effects are also analyzed. The intention-to-treat analyses are performed for the outcomes. SPSS 25 software (IBM SPSS Statistics, New York, USA) is used for the data analyses. Data analyses are conducted by a data analyst who is unaware of allocation and treatment.

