Our preliminary study revealed that the modulus of elasticity of the lateral femoral muscle was significantly higher on the affected side than on the healthy side in patients with KOA (*p* < 0.01). It was also found that FSN significantly improved symptoms and signs while reducing the modulus of elasticity of the lower limb skeletal muscles (vastus lateralis, tibialis anterior, and gastrocnemius) of KOA patients (*p* < 0.05), and a related paper is being prepared for publication. Previously, two studies have suggested that FSN therapy applied for the treatment of KOA effectively relieved pain [22, 23]. However, both studies only applied pain-related measures or function-related measures as indicators of efficacy. Few studies have focused on a biomechanical point of view. There are also few published clinical studies that have used objective measures other than scales, such as ultrasonography or imaging. Therefore, the objective of this randomized clinical trial is to investigate the clinical effects and biomechanical mechanisms of FSN for the treatment of elderly patients with knee osteoarthritis. We hypothesized that an intervention programme using FSN for 2 weeks, 3 times per week, would produce better improvements in pain as well as physical function of the knee compared to a positive control group taking celecoxib. Furthermore, this clinical trial also aims to evaluate the ability of FSN to improve gait and lower limb muscle flexibility, which may further help explore the mechanism of FSN therapy.

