### Sample size calculation

The main outcome measure of this study is the decrease in VAS score from baseline during the 2-week treatment period. FSN, an emerging acupuncture method, has been studied in randomized controlled trials [22, 23]. However, both of these previous studies used superiority testing, which cannot provide an appropriate reference for the sample size calculation of our study. Therefore, we refer to a randomized controlled trial that compared electroacupuncture with an NSAID for treating KOA [26]. We assume that the effect sizes of interventions (FSN and celecoxib) in this trial were similar to those (acupuncture and diclofenac applied for interventions) in the aforementioned study. The results of the above study showed that the VAS score decreased by 48.24 ± 3.59 mm from baseline after 4 weeks of electroacupuncture treatment, and by 32.99 ± 3.94 mm from baseline after 4 weeks of oral administration of diclofenac. The actual difference in the VAS score between the two interventions after 4 weeks of treatment was 15.25 mm, with a combined standard deviation of 3.85 mm. However, since the course of treatment in our trial is half of that in the aforementioned study, appropriate adjustments for the expected difference in the VAS score are needed. Based on our clinical experience, the efficacy and the treatment period cannot be considered to increase in full equivalence, and since the 2-weeks intervention course is relatively short, we would not expect the cumulative efficacy to be half that of the 4-weeks intervention in the aforementioned study.

Therefore, to compare the efficacy of FSN and celecoxib, we assume that the difference in two groups’ means of the changes in the VAS score is 6.5 mm after 2 weeks of treatment, which is slightly less than half the difference observed in the reference trial [26] after 4 weeks of intervention. Assuming a 1:1 ratio of participants in the 2 groups, the NIM (Non-Inferiority Margin) is defined as 10 mm. A two-sided test with a significance level (α) of 0.05 and a power(1-β) of 0.80 is applied. With a possible dropout rate of 10%, using the PASS 15.0 software, 60 participants shall be included in this study.

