## Conclusion

The hypothesis of this study is that FSN therapy has a more significant and long-term effect on pain relief and improvement of joint function than conventional oral celecoxib in elderly patients with KOA. We aim to test this hypothesis through a rigorous clinical trial. We anticipate that the results of this study will provide guidance for the clinical application and promotion of FSN therapy in KOA. Furthermore, the preliminary analyses may help to further explore the rationale and potential indications of FSN.

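### The 10 mm non-inferiority margin used to size the trial is never used in the analysis, which tests only for a difference while the hypothesis is superiority

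*Protocol article*

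**What the plan says.** The protocol article treats the primary comparison in three ways.

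- **Sizing.** Sample size calculation sets the earlier FSN trials aside because "both of these previous studies used superiority testing, which cannot provide an appropriate reference for the sample size calculation of our study". It then states that "the NIM (Non-Inferiority Margin) is defined as 10 mm". The same section assumes that the difference in "means of the changes in the VAS score is 6.5 mm after 2 weeks of treatment" and cites a reference trial "with a combined standard deviation of 3.85 mm". It uses a two-sided 0.05 level, 80% power and 10% dropout, and arrives at 60 participants.
- **Hypothesis.** The Introduction expects that FSN "would produce better improvements in pain as well as physical function of the knee compared to a positive control group taking celecoxib". The Conclusion gives the hypothesis as "FSN therapy has a more significant and long-term effect on pain relief and improvement of joint function than conventional oral celecoxib". Both are superiority statements.
- **Analysis.** Statistical analysis says "All the statistical tests are conducted using a bilateral test", with P<0.05 as the criterion for a difference. Between-group comparisons use an independent-samples t test or a Mann–Whitney U test. On the analysis population it says "The intention-to-treat analyses are performed for the outcomes".

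The margin appears only in Sample size calculation. The introduction to the Abstract adds another framing: whether FSN's effect is comparable to that of commonly used drugs.

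**The concern.** A non-inferiority margin has meaning only if an analysis compares a confidence limit with it. Here the analysis section sets a decision rule for every test, and that rule concerns a difference from zero.

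This matters for three of the possible outcomes:

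- **P>0.05.** The plan gives no reading. Because the Abstract asks about comparability with drugs, a non-significant P could be reported as similarity without a 10 mm loss having been excluded.
- **P<0.05 favouring celecoxib.** The whole interval may still lie inside 10 mm. The difference rule then says FSN is worse and the margin rule says it is non-inferior, and the plan does not say which governs.
- **Non-inferiority achieved without superiority.** This is the result the margin was set for, and no rule exists to declare it.

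With no rule fixed in advance, the framework could be chosen after the data are seen. Participants are unblinded and the primary outcome is self-reported, so that freedom should be closed.

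**Working it through.** **Inputs.** From Sample size calculation: margin 10 mm, assumed difference 6.5 mm, SD 3.85 mm (from the reference trial), two-sided 0.05, 80% power, 10% dropout, 30 per arm. Evaluable per arm: 30 × 0.9 = 27, so df = 2 × 27 − 2 = 52 and t(0.975, 52) = 2.007. SDs of 10, 15 and 20 mm are assumptions to show a range; the article does not give them.

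**The plan's own figure.** Per-arm n is the smallest giving the required power by noncentral t at one-sided 0.025 and SD 3.85, then divided by 0.9 and rounded up.

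| Framework | Distance to null | Power | n per arm | Total with dropout |
|---|---|---|---|---|
| Non-inferiority, FSN 6.5 mm better | 10 + 6.5 = 16.5 | 80% | 3 | 8 |
| Non-inferiority, no true difference | 10 | 80% | 4 | 10 |
| Superiority | 6.5 | 80% | 7 | 16 |
| Non-inferiority, FSN 6.5 mm worse | 10 − 6.5 = 3.5 | 80% | 21 | 48 |
| Non-inferiority, FSN 6.5 mm worse | 3.5 | 90% | 27 | 60 |

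At the stated 80% power none of these gives 60. In this table 60 appears only when the 6.5 mm counts against FSN and power is 90%, which the text does not state. This is a separate problem. It is relevant here because 60 does not reveal which hypothesis the trial was sized for.

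**Precision and power of the two rules with 27 per arm.**

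- Standard error = SD × √(2/27). At SD 20: 20 × 0.2722 = 5.44 mm.
- 95% CI half-width h = 2.007 × SE. At SD 20: 2.007 × 5.44 = 10.9 mm.
- Power = P(T > 2.007), with T noncentral t on 52 df and noncentrality distance/SE. The distance is 6.5 mm for the difference test, 16.5 mm for the margin test with a true 6.5 mm gain, and 10 mm for the margin test with no true difference.

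| SD (mm) | h (mm) | Difference test, true gain 6.5 | Margin test, true gain 6.5 | Margin test, true difference 0 |
|---|---|---|---|---|
| 3.85 (article) | 2.1 | about 100% | about 100% | about 100% |
| 10 (assumed) | 5.5 | 65% | about 100% | 95% |
| 15 (assumed) | 8.2 | 35% | 98% | 67% |
| 20 (assumed) | 10.9 | 22% | 84% | 44% |

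**What a non-significant P says about the margin.** Let d be the observed advantage of FSN. P>0.05 means −h < d < h. Non-inferiority needs d − h > −10, that is d > h − 10.

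- SD 3.85: d > 2.1 − 10 = −7.9. Every non-significant result satisfies this. A result between −7.9 and −2.1 significantly favours celecoxib and is still inside the margin.
- SD 10: d > −4.5. A non-significant d between −5.5 and −4.5 does not exclude a 10 mm loss.
- SD 15: d > −1.8. A non-significant d between −8.2 and −1.8 does not.
- SD 20: d > 0.9. A non-significant d anywhere from −10.9 to 0.9 does not.

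**The case against.** **On the plan's own figures the conflict may not bite.** A significant t test favouring FSN also establishes non-inferiority. With 6.5 mm and SD 3.85 that test has essentially 100% power. This stands. A reader might infer that no planned analysis could deliver the conclusion the trial was sized for; the documents do not support that. The t test's confidence interval could also be set against 10 mm, but nothing plans it.

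**The power contrast depends on assumptions.** The 22% versus 84% gap holds only at an assumed SD of 20 mm with a true 6.5 mm gain. With no true difference the margin test has 44% power there. This is why a range is shown.

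**The margin's size.** A reader might scale the reference trial's diclofenac change (32.99 mm) to two weeks and infer that 10 mm gives away most of celecoxib's effect. That does not follow. The scaling ratio comes from between-group differences, while 32.99 mm is a within-arm change from baseline, not an effect over placebo. The article gives no placebo-controlled figure, so no tighter margin can be derived from it.

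**Rank tests.** A reader might infer that Mann–Whitney cannot be used with a margin in mm. Under a location shift, a margin-shifted rank test or a Hodges–Lehmann interval can be. The article does not specify either.

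**Analysis sets.** Naming only intention-to-treat is not an error in a condensed article, since further sets are commonly left to a SAP. A per-protocol analysis is a recommendation here.

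**Could the rest be left to a SAP?** No. The article states a rule for all tests, and that rule does not match its sizing. A SAP that followed it would contain no non-inferiority test; one that added such a test would depart from the article's rule and its stated hypothesis.

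**Conclusion.** The concern holds in this limited form. The sizing is non-inferiority with a 10 mm margin, the stated hypothesis is superiority, and the only decision rule is a two-sided difference test that never uses the margin. A win for FSN on that test is interpretable under either framework. A non-significant result, or one favouring celecoxib, has no stated meaning against the margin.

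The practical size depends on the true SD. At the article's 3.85 mm, both rules have power near 100% for a 6.5 mm gain, and the gap shows mainly when celecoxib is moderately better. At assumed SDs of 10 to 20 mm, power for the same gain is 65% to 22% by the difference rule and about 100% to 84% by the margin rule, and some non-significant results leave a 10 mm loss open. These figures assume 27 evaluable per arm, equal SDs and a t-based analysis.

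The rule should be settled before the data are analysed, because it determines what the primary result means.

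**What to change.** State one primary rule in Statistical analysis:

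1. Estimate the between-group difference in VAS change from baseline to day 14 with a two-sided 95% CI. Conclude non-inferiority if the limit unfavourable to FSN is inside the 10 mm margin.
2. Only then claim superiority, if the same CI excludes 0 in favour of FSN. This fixed sequence has no alpha cost.
3. If a rank method is used, report a Hodges–Lehmann interval and set that against the margin.
4. State that P>0.05 is not evidence of similarity.
5. Add a per-protocol analysis of the primary outcome as a supportive check.

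Then align the other sections. The Introduction and Conclusion should present superiority on pain as the second step. Sample size calculation should name the primary hypothesis, the direction of the 6.5 mm and the SD used.

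The cost is wording and one extra analysis run. The rule itself needs no new patients or measurements.
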